### Secondary endpoints

Comparative analysis of RISE as predictor of LTx-free survival in subgroups stratified by age; gender; baseline lung function; baseline 6MWD; baseline extent of fibrosis on HRCT; time between onset of symptoms and diagnosis; presence of APH; presence of concomitant emphysema; presence of comorbidities (COPD, CAD, LHD, SA); participating site.Clinical progression, as a predictor of mortality, defined as either: absolute decline of FVC >10% pred; decline of 6-min walk distance >50 m; hospitalization for respiratory causes; LTx assessment; or death.Incidence of AEs of IPF and its predictors, if any.Incidence of hospitalizations due to respiratory causes and its predictors, if any.LTx-free survival, incidence of AEs, incidence of hospitalizations, and time to progression of patients with HRCT pattern definite/probable for UIP vs. patients with indeterminate/inconsistent pattern. In this subanalysis, 2 groups of patients matched for age, gender, BMI, and extent of fibrosis at the time of diagnosis will be considered.LTx-free survival, incidence of AEs, incidence of hospitalizations, and time to progression of patients with autoimmune markers (although not meeting criteria for interstitial pneumonia with autoimmune features [23] versus those without. In this subanalysis, 2 groups of patients matched for age, gender, BMI and extent of fibrosis at the time of diagnosis will be considered.LTx-free survival, incidence of AEs, incidence of hospitalizations and time to progression of patients with concomitant emphysema versus those without. In this subanalysis, 2 groups of patients matched for age, gender, BMI and extent of fibrosis at the time of diagnosis will be considered.LTx-free survival, incidence of AEs, incidence of hospitalizations and time to progression of patients treated with pirfenidone versus patients treated with nintedanib. In this subanalysis, 2 groups of patients matched for age, gender, BMI and extent of fibrosis at the time of diagnosis will be considered.LTx-free survival, incidence of AEs, incidence of hospitalizations and time to progression of patients whose therapy was switched (from pirfenidone to nintedanib and viceversa). In this subanalysis, 2 groups of patients matched for age, gender, BMI and extent of fibrosis at the time of diagnosis will be considered.6MWD m versus % pred as predictors of mortality.Survival, incidence of AEs and time to progression on the LTx waitlist of listed patients.Time to progression in patients with initially non-clinically significant disease.Long-term follow-up (beyond 3 years) of patients who are still alive without a LTx, until required recruitment is completed. This will include LTx-free survival, incidence of AEs, incidence of hospitalizations and time to progression.

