## Methods and design

This is an observational, international, prospective cohort study including 2 large tertiary referral centres for interstitial lung disease (ILD) (London, Canada and Rome, Italy). The study was designed to reflect common clinical practice in IPF.

Only patients newly diagnosed with IPF based on the American Thoracic Society/European Respiratory Society (ATS/ERS) criteria [1] and local multi-disciplinary discussion (MDD) [18] at participating centres will be included in the study. As a further inclusion step, for all patients who did not undergo a surgical lung biopsy (SLB), a panel of 3 chest radiologists with ILD expertise will examine each HRCT, and patients will be included, if at least 2 out of 3 agree on a pattern of probable/definite UIP. For patients who underwent a SLB, a panel of 3 lung pathologists with ILD expertise will examine each biopsy, and patients will be included if at least 2 out of 3 agree on a pattern of probable/definite UIP.

All known causes of ILD will carefully excluded before each patient is included in the study. These include domestic, environmental, occupational, exposures; drug-induced lung toxicity; and connective tissue diseases. Comorbidities considered will include APH (only if right heart catheterization[RHC]-proven), chronic obstructive pulmonary disease (COPD), coronary artery disease (CAD), left heart dysfunction (LHD), and sleep apnea (SA).

A development cohort and a validation cohort will be included in the study. In both cohorts, at the first visit (time of diagnosis) and at each subsequent visit at 4-month intervals, for a period of 3 years, MRCDS (Table 1), pulmonary function tests (PFTs)(forced expiratory volume during the first second [FEV_1_], FVC, diffusing lung capacity for carbon monoxide [DLCO]), and 6MWD will be obtained. 6MWD % predicted will be calculated, as previously described [19]. The use of supplemental oxygen and the level of oxygen desaturation will be considered. The following events will be recorded in the study: death; LTx referral; LTx; AEs; hospitalization for respiratory causes; start, stop and switch of anti-fibrotic therapy; start of supplemental home oxygen therapy; start and stop of physiotherapy program enrolments; progression of disease (see Secondary endpoints).

**Table 1 Tab1:** MRC dyspnea score (0 to 5 scale) [20]

Grade	Description
0	I only get breathless with strenuous exercise

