### Primary endpoint

Three-year, LTx-free survival from the time of diagnosis, measured as the time between diagnosis and death from any cause, or LTx. Once they receive a LTx, patients will be censored. Since mortality and LTx are competing events, a Fine-Gray competing risk regression analysis will be used. Please refer to the statistics section for details.

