### Statistical analysis and sample size calculation

The distribution of variables considered will be analysed with Kolmogorov–Smirnov test. Interobserver variability among chest radiologists and lung pathologists will be assessed with Weighted kappa coefficients [29]. Survivors and non-survivors will be compared by using the unpaired t-test, or, for not normally distribute variables, with the Mann–Whitney U-test. To rule out multicollinearity and demonstrate that included variables are truly independent, variance inflation factors of the RISE components will be calculated [30]. Receiver operating characteristics analysis will be used to identify the most accurate cut-off values for each variable to predict endpoints. Multivariate analysis of significant predictors of endpoints will be conducted with the Cox proportional hazard model. Results will be summarized as hazard ratios. Once patients are listed for LTx, death and LTx become competing events. To account for the competing risks of LTx and death in the population of patients undergoing LTx assessment, the Fine-Gray competing risk regression model [31] will be used. This will identify variables significantly predicting independent survival status and results will be summarized as subdistribution hazard ratios. These represent the relative risk of dying prior to LTx. Survival will be further evaluated using Kaplan–Meier curves and the log-rank test. Sample size calculation for an observational, cohort study was conducted using the methodology described by Wang and Ji [32], with the assistance of a statistician. Using available, preliminary data on 109 patients, dropout rate, ratio of low RISE to high RISE, and mortality rates in low RISE and high RISE subgroups were determined. With a power (probability of detecting a real effect) of 90%, and with a conservative approach, a sample size of 125 patients for each cohort was determined to be required.

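### Clinical progression is listed as a predictor of mortality, but its definition counts death as progression

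*Protocol article*

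**What the plan says.** The Secondary endpoints section of the protocol article gives this item its role and its definition in one sentence. The role is "Clinical progression, as a predictor of mortality, defined as either". The list that follows starts with an absolute FVC fall of more than 10% predicted and continues "decline of 6-min walk distance >50 m; hospitalization for respiratory causes; LTx assessment; or death". Any one of the five suffices.

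The Methods and design section does not define progression separately. Its list of recorded events points back to the same place: "progression of disease (see Secondary endpoints". The same section of secondary endpoints also uses time to progression as an outcome in several matched comparisons.

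The Primary endpoint section does not use progression. LTx-free survival is "measured as the time between diagnosis and death from any cause, or LTx".

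On modelling, the Statistical analysis and sample size calculation section says "Multivariate analysis of significant predictors of endpoints will be conducted with the Cox proportional hazard model". It also names ROC cut-offs, survivor versus non-survivor comparisons, Fine-Gray regression, Kaplan-Meier curves and the log-rank test. It mentions neither a landmark nor a covariate updated over time.

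**The concern.** A predictor has to be able to be absent in a patient who goes on to have the outcome. Under this definition it cannot be: a patient who dies without any earlier FVC fall, walk-distance fall, respiratory hospitalization or transplant assessment becomes a progressor by dying. The group without progression is emptied of deaths by the definition and not by the biology.

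At stake is the meaning of the result. The analysis should show whether a measurable, non-fatal deterioration signals later death. If death is left in the predictor, a strong association could be reported when the non-fatal components carry no information, and the reader could not tell that result from a real one. This matters in a study that aims to support clinical decisions on treatment and transplant timing.

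Death is an ordinary component when progression is the outcome, as in the time-to-progression comparisons. The fault lies in one definition serving both roles.

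**Working it through.** The protocol article states no figure for this analysis, so there is none to reproduce. The check is of the definition, followed by an illustration of its size.

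**Step 1: the definition.** Let D be death during follow-up and P any of the four non-fatal components. The predictor as written is X = P or D. If D is true, X is true. Hence, with ever/never coding, Pr(D | not X) = 0 for any relation between P and D. An ever/never odds ratio or Cox hazard ratio then has an empty cell (no deaths in the reference group) and no finite estimate.

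**Step 2: a worked table.** The cohort size comes from the document ("a sample size of 125 patients for each cohort was determined to be required"). The 50 deaths and the 40% are assumptions. Suppose P is unrelated to death and occurs in 40% of patients.

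| Predictor | Progressors | Deaths among them | Non-progressors | Deaths among them |
|---|---|---|---|---|
| As written (P or death) | 50 + 0.40 × 75 = 80 | 50 (62.5%) | 125 − 80 = 45 | 0 (0%) |
| Non-fatal only (P) | 0.40 × 125 = 50 | 0.40 × 50 = 20 (40%) | 125 − 50 = 75 | 50 − 20 = 30 (40%) |

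The second row shows the truth that was assumed: no association. The first row shows the same patients with death added to the predictor.

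**Step 3: a range.** With mortality d and non-fatal progression p independent of each other, the proportion classed as progressors is p + (1 − p)d, and mortality among them is d / [p + (1 − p)d]. Assumed ranges, not taken from the document, are d from 20% to 50% and p from 30% to 70%.

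- d = 0.20, p = 0.70: 0.20 / (0.70 + 0.30 × 0.20) = 0.20 / 0.76 = 26.3%
- d = 0.35, p = 0.50: 0.35 / (0.50 + 0.50 × 0.35) = 0.35 / 0.675 = 51.9%
- d = 0.50, p = 0.30: 0.50 / (0.30 + 0.70 × 0.50) = 0.50 / 0.65 = 76.9%

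In every case the comparison is with 0% among non-progressors.

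**Step 4: how often a null effect would be called significant.** The null was simulated over that grid with 125 patients, 2,000 runs per scenario, ever/never coding and a two-sided Fisher exact test at 0.05. With death in the definition, the test rejected in 99.8% to 100% of runs. With death removed, it rejected in 3.2% to 5.1%. The simulation ignores the timing of events, so it isolates the effect of including death and nothing else.

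**The case against.** The strongest reply is that the article does not prescribe ever/never coding. It names Cox regression, and data are collected at 4-month visits. If progression were counted only when it comes before death, or were fixed at a landmark among patients still alive, the death component would have no effect. A condensed article may leave such coding to a fuller document. This stands in part: 0% mortality among non-progressors and an infinite ratio follow under ever/never coding, and the document does not commit to it. It does not remove the fault. The article states the composite explicitly, with death in it, for use as a predictor. If landmark or time-dependent coding is intended, the words about death do nothing in this role and should still come out.

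A second reply is that the sentence may mainly define progression for the time-to-progression outcomes, where including death is normal. That is plausible, and a deliberately circular analysis should not be presumed. But the sentence names the predictor role, and no other definition is offered for it.

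A reader might also infer that the waitlist analysis, "Survival, incidence of AEs and time to progression on the LTx waitlist of listed patients", fails because every listed patient has already met the transplant-assessment component. The document does not support that. Time to progression on the waitlist naturally means events after listing, and FVC decline, walk-distance decline, respiratory hospitalization and death can all still occur then. Nothing in the text says that an event before listing removes a patient from risk.

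**Conclusion.** The point holds in a limited form. The stated definition places the outcome inside the predictor, and the article gives no death-free definition, landmark or time-dependent coding to separate them. Under ever/never coding the consequence is complete: non-progressor mortality is 0% regardless of the non-fatal components. In the assumed scenarios with no true association, progressor mortality runs from 26% to 77%. Those percentages and the rejection rates rest on assumed mortality and progression rates, on independence and on ever/never coding. The 0% rests on the definition and that coding alone.

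It would go too far to say that the association is guaranteed whatever the analysis, since coding that counts only progression before death avoids the problem. It would also go too far to say that the study's main result is compromised. The fault touches one secondary analysis. The primary endpoint and the analyses of RISE as a predictor of it do not use composite progression. The wording should be corrected before analysis, but the point does not threaten the trial's main conclusion.

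**What to change.** State two definitions in the Secondary endpoints section.

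1. **Progression as a predictor of mortality:** FVC decline, 6MWD decline or respiratory hospitalization, with or without LTx assessment, and without death. Enter it either as a time-dependent covariate that changes at the first non-fatal event before death, or as status at a stated landmark visit among patients alive at that visit, with mortality counted from then on. Removing death while keeping ever/never coding over the whole follow-up would not be enough, because patients who live longer have more visits at which to be classed as progressing.
2. **Progression as an outcome (time to progression):** the present composite, including death.

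The cost is a few lines of wording. FVC and 6MWD are measured at each visit, and respiratory hospitalizations and deaths are already recorded. If LTx assessment is kept in the predictor, its date should be confirmed as collected: the list of recorded events in Methods and design names LTx referral and LTx but not assessment separately. No change to recruitment, sample size or the primary analysis follows.

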1	I get short of breath when hurrying on level ground or walking up a slight hill
2	On level ground, I walk slower than people of the same age because of breathlessness
3	On level ground, I have to stop for breath when walking at my own pace
4	I stop for breath after walking about 100 m or after 5 min on level ground
5	I am too breathless to leave the house or I am breathless when dressing

The RISE (Table 2) will be first calculated, as previously described, on a scale from 1 to 3 [3]. However, a modified and improved version of the RISE will also be considered, using the CALIPER-revised CPI instead of the original version of CPI [13], and with a new 1 to 4 scale, which may allow for better stratification for mortality risk (Table 2). If superior to the previous version of RISE, the modified version will be tested for validation.

**Table 2 Tab2:** Risk Stratification Score (RISE) (revised)

RISE components: 1. MRCDS ≥ selected cutoff* 2. 6MWD % pred ≤ selected cutoff* 3. CPI ≥ selected cutoff*	RISE
No parameter met	0
One parameter met	1
Two parameters met	2
Three parameters met	3

MRCDS: MRC dyspnea score; 6MWD: 6-min walk distance; CPI: Composite Physiologic Index (CALIPER-revised version)

^*^selected cut-offs for each variable will be determined by receiver operating characteristics analysis (c-statistics)

Patients will be prospectively followed for a period of 3 years from the time of diagnosis and enrolment. All multi-dimensional scores will be calculated at 4-months intervals corresponding to each visit. A 2nd HRCT will be obtained at the 2-year visit, or sooner if clinically indicated, and as per clinicians’ discretion. The HRCT fibrosis score [12] will be then recalculated on the 2nd scan. Deaths, LTx, AEs and hospitalizations due to respiratory causes will be recorded. All protocol violations (missed visits, delayed visits, data not obtained at individual visits) will be systematically recorded. Every interruption or change in course of therapy will be recorded. When available, hemodynamic data from RHCs will be considered. Since 2D echocardiograms alone are unreliable in predicting the presence of APH in IPF [21], they will not be considered.

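### Clinical progression is named as a predictor of mortality, but its definition includes death, so predictor and outcome overlap; this use needs a non-fatal definition

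*Protocol article*

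**What the plan says.** The protocol article, under Secondary endpoints, introduces the item as "Clinical progression, as a predictor of mortality, defined as either" and then lists the components: an absolute FVC decline of more than 10% predicted, followed by "decline of 6-min walk distance >50 m; hospitalization for respiratory causes; LTx assessment; or death". One sentence thus assigns progression the role of predictor, names mortality as the outcome, and puts death among the components.

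No second definition is given. The list of recorded events in Methods and design has "progression of disease (see Secondary endpoints"), which points back to the same sentence. Later items under Secondary endpoints use time to progression as an outcome and do not redefine it.

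On analysis, the section Statistical analysis and sample size calculation says "Multivariate analysis of significant predictors of endpoints will be conducted with the Cox proportional hazard model" and "Survivors and non-survivors will be compared by using the unpaired t-test". It also plans ROC analysis, Kaplan-Meier curves and the log-rank test. It does not say how a predictor that arises during follow-up is to be placed in time relative to death. Follow-up is fixed: "Patients will be prospectively followed for a period of 3 years from the time of diagnosis and enrolment".

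**The concern.** A composite that includes death is a sound outcome: time to progression or death is ordinary progression-free survival. It is not a sound exposure when death is the outcome, because a patient can then enter the exposed group by having the outcome.

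The question at stake is whether a patient who has progressed without dying is at higher risk of death afterwards. The Background motivates the study by the limits of current ways of detecting progression, and the hypothesis is framed in terms of sensitivity and specificity. An apparent sensitivity of 100% for this composite could be read as a clinical finding when it only restates the definition.

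**Working it through.** The article reports no figure for this endpoint, so there is none to reproduce. The check follows from the definition, with assumed rates used only to show size.

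**Inputs.** From the article: the five components and the role as predictor (Secondary endpoints), 3 years of follow-up (Methods and design), and 125 patients per cohort (Statistical analysis and sample size calculation). Assumed: d, the 3-year probability of death, and p, the share of patients with non-fatal progression, taken as independent of death so that the true association is nil.

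**Step 1: ever/never classification, death included.** Expected proportions are:

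| | Died | Alive |
|---|---|---|
| Ever progressed | d | (1 - d)p |
| Never progressed | 0 | (1 - d)(1 - p) |

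The zero cell follows from the definition and needs no assumed rate. Hence sensitivity = d/d = 100%, negative predictive value = 100%, specificity = 1 - p, and the odds ratio is infinite. A Cox model using this indicator as a fixed covariate has no deaths in the never-progressed group, so its hazard ratio has no finite estimate.

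**Step 2: AUC.** For a binary marker, AUC = (sensitivity + specificity)/2 = (1 + 1 - p)/2 = 1 - p/2.

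| p | AUC, death included | AUC, death removed |
|---|---|---|
| 30% | 0.85 | 0.50 |
| 40% | 0.80 | 0.50 |
| 50% | 0.75 | 0.50 |
| 60% | 0.70 | 0.50 |

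**Step 3: risk of death by group.** Among the ever progressed, risk = d/[d + (1 - d)p].
- d = 0.45, p = 0.5: 0.45/(0.45 + 0.275) = 0.62
- d = 0.30, p = 0.6: 0.30/(0.30 + 0.42) = 0.42
- d = 0.63, p = 0.4: 0.63/(0.63 + 0.148) = 0.81

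Among the never progressed it is 0 each time; with death removed it is d in both groups. The values 0.45 and 0.63 are 1 - exp(-3/5) and 1 - exp(-3/3). They apply a constant hazard to the mean survival of 5 and 3 years that the Background gives for untreated disease. The value 0.30 is an assumption for treated patients.

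**Step 4: a test in a cohort of 125.** In a simulation with no true association, d was 20%, 35% or 50% and p was 30%, 50% or 70% (2,000 runs per setting, Fisher exact test, two-sided 0.05). With death in the predictor, 99.8% to 100% of runs were significant. With death removed, 3.2% to 5.1% were.

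**Step 5: a different coding.** Suppose progression is time-updated in a Cox model and read just before each event. A patient whose first component is death then counts as a death without prior progression. The never-progressed group has deaths and the hazard ratio is finite. Under this coding the death component has no effect, so removing it loses nothing; under the ever/never coding it creates the association.

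**The case against.** The strongest defence is that this sentence is the only place where the composite is defined and must also serve the time-to-progression outcomes, where death belongs. The mention of mortality could then be a remark on prognostic relevance. This does not hold up well. The same list uses the predictor wording for RISE and for walk distance in metres versus percent predicted, and Methods and design says variables will be tested as predictors of mortality. In each case the phrase names the exposure in an analysis. What stands is that death is a legitimate component wherever progression is the outcome.

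The second objection stands in full. Steps 1 to 4 assume ever/never classification over follow-up, which the article does not specify. It names Cox regression, and Step 5 shows that a time-updated covariate gives a finite and interpretable hazard ratio. The coding of such a covariate is commonly left to an analysis plan, so its absence here is not itself a fault. A reader might infer that the result must be circular whatever analysis is run; the article does not support that.

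A reader might also infer that the study could not show whether FVC or walk-distance decline predicts death. That too goes too far. Methods and design tests FVC and walk distance individually as predictors of mortality, and the Abstract says longitudinal changes of each variable will be assessed.

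Finally, the values of d and p are illustrative. The survival figures behind 45% and 63% refer to untreated patients, while this study includes treated ones.

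**Conclusion.** The definition is wrong as written for this one use: the predictor contains its outcome, and the article offers no alternative definition. This is a stated rule that needs changing, not a detail left for later.

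The consequence is conditional. Under ever/never classification, 100% sensitivity and zero deaths among non-progressors follow from the definition alone. The AUC of 0.70 to 0.85, the 42% to 81% risk among progressors and the near-certain significance also rest on the assumed d and p and on independence. Under a time-updated or landmark analysis confined to progression before death, these distortions do not arise.

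The matter should be fixed but is not critical to the trial. It affects one item in a long secondary list. It does not touch the primary endpoint, "measured as the time between diagnosis and death from any cause, or LTx", the development and validation of RISE, or the sample size.

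**What to change.** Separate the two uses in the endpoint definition.

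- For progression as a predictor of mortality, use only the non-fatal components: FVC decline, walk-distance decline, respiratory hospitalization and LTx assessment. Date progression at the first of these before death. Enter it as a time-dependent covariate, or classify it at a fixed landmark among patients still alive, with later death as the outcome. The timing rule is still needed once death is removed, because patients who live longer have more time to progress.
- For the time-to-progression endpoints, keep death in the composite.

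The cost is one sentence in the article or analysis plan and a small programming change. One data item needs confirming: the recorded events in Methods and design include LTx referral and LTx, whereas the progression component is LTx assessment. The date of assessment should be confirmed as captured. A sensitivity analysis that sets aside components first recorded during a terminal admission is optional.

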The Gender-Age-Physiology (GAP) index considers gender, age, FVC (% predicted) an DLCO (% predicted) to stratify patients in 3 different stages of the disease. This model was validated with a 3-year retrospective study using 3 different cohorts (558 patients), and it was shown to predict mortality in patients with IPF [4]. However, 3 different studies demonstrated that longitudinal changes of GAP performed poorly in predicting survival [11, 46, 47]. The use of (relatively) fixed variables such as gender and age and the lack of prospective validation may explain these limitations.

The MRSS with Ascertainable Predictors (accounting age, history of respiratory hospitalization, FVC [% predicted] and 24-week change in % predicted FVC), was studied in a 1-year prospective clinical trial with 830 participants [17]. A longer follow-up will be needed to adequately capture mortality in IPF. A potential concern in this score is the use of hospitalization as a parameter, given that criteria for hospital admission vary in different institutions, potentially compromising reproducibility.

An encouraging finding was that multi-dimensional indices (RISE, CPI and GAP) proved their effectiveness even in patients undergoing LTx assessment [9], with an accuracy in predicting mortality similar to the Lung Allocation Score, which is commonly used to evaluate patients on LTx waiting lists, but is much more complex to calculate [48, 49].

The use of multi-dimensional indices as clinical trials endpoints is another, crucially important, potential application of multi-dimensional indices. The search for new therapies in IPF in the immediate future will be particular challenging, as most treatments are only able to slow down an occurring progression of disease, making it very difficult to capture a clinically significant difference. This further points to the limitations of FVC decline as only endpoint measure, and, at the same time, to the advantage of using parameters that better capture pathophysiology and clinical status in IPF, but are still easily repeatable. A preliminary study on RISE as a parameter to longitudinally capture response to pirfenidone indeed yielded encouraging results [11].

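### One respiratory admission counts as progression, and the matched comparisons leave out site, so a difference in admission practice between the two centres can appear as a group difference

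*Protocol article*

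**What the plan says.** All references are to the Protocol article.

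- **Definition (Secondary endpoints).** The item reads "Clinical progression, as a predictor of mortality, defined as either: absolute decline of FVC >10% pred; decline of 6-min walk distance >50 m" and continues "hospitalization for respiratory causes; LTx assessment; or death". Any one event suffices. No severity or admission criterion is attached to the hospitalization component.
- **Use as an outcome (Secondary endpoints).** Time to progression and incidence of hospitalizations are outcomes in five matched sub-analyses: HRCT pattern, autoimmune markers, concomitant emphysema, pirfenidone versus nintedanib, and switch of therapy. For the HRCT-pattern item the rule is that "2 groups of patients matched for age, gender, BMI, and extent of fibrosis at the time of diagnosis will be considered". The other four name the same four factors.
- **Use as a predictor (Secondary endpoints).** Progression is also to be examined as a predictor of mortality.
- **Setting (Methods and design).** There are two tertiary referral centres, one in Canada and one in Italy.
- **Remark on admissions (Discussion).** The competing Mortality Risk Scoring System (MRSS) is faulted for including hospitalization, because "criteria for hospital admission vary in different institutions, potentially compromising reproducibility".
- **Where site is considered (Secondary endpoints).** Participating site closes the list of factors in the item that begins "Comparative analysis of RISE as predictor of LTx-free survival in subgroups stratified by age; gender; baseline lung function". It is not mentioned for the progression or hospitalization comparisons.

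**The concern.** The groups in the five sub-analyses are not formed by randomisation, so comparability rests on the matching. The matching list is explicit and omits site. Two of the outcomes depend partly on a decision to admit, which the protocol's own Discussion describes as varying between institutions.

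Two conditions together would create bias: the compared groups draw on the two centres in different proportions, and the centres admit at different thresholds for the same clinical state. Drug choice is the most plausible route, because the study does not assign treatment. A difference in admission practice would then be read as a difference between pirfenidone and nintedanib in hospitalization incidence and time to progression.

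For progression as a predictor of mortality, admissions made at a lower threshold at one centre could add events that carry less prognostic information there. An unstratified analysis would not show this.

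**Working it through.** No stated figure in the plan bears on this point, so there is none to reproduce. The check has two parts.

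**1. The text.** The definition lets a single admission count. The matching list is age, gender, BMI and extent of fibrosis. Site appears only as a subgroup factor for RISE and LTx-free survival. The Statistical analysis and sample size calculation section names no site adjustment. The stated rule therefore does not protect the progression and hospitalization comparisons from a site effect.

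**2. The possible size.** Every rate here is an assumption; the documents give none. Suppose disease is the same at both centres and there is no true group effect. Let

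- hA, hB = 3-year probability of respiratory hospitalization at centres A and B;
- q = probability of meeting another progression criterion, the same at both centres and independent of hospitalization;
- p = share of group 1 from centre B, with group 2 the mirror image (1 − p from centre B).

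Then

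- spurious hospitalization difference = (2p − 1)(hB − hA);
- progression at a centre = 1 − (1 − q)(1 − h);
- spurious progression difference = (2p − 1)(1 − q)(hB − hA).

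Example with hA = 25%, hB = 40%, q = 45%, p = 0.7:

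- Hospitalization in group 1: 0.7 × 40% + 0.3 × 25% = 35.5%. In group 2: 0.3 × 40% + 0.7 × 25% = 29.5%. Difference: 6.0 points.
- Progression at centre A: 1 − 0.55 × 0.75 = 58.75%. At centre B: 1 − 0.55 × 0.60 = 67.0%. Centre gap: 8.25 points. Group difference: 0.4 × 8.25 = 3.3 points.

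Spurious differences in percentage points, q = 45%:

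| Split by site | Hospitalization, 25% vs 40% | Progression, 25% vs 40% | Hospitalization, 20% vs 40% | Progression, 20% vs 40% |
|---|---|---|---|---|
| 50/50 | 0 | 0 | 0 | 0 |
| 55/45 | 1.5 | 0.8 | 2.0 | 1.1 |
| 60/40 | 3.0 | 1.65 | 4.0 | 2.2 |
| 70/30 | 6.0 | 3.3 | 8.0 | 4.4 |
| 80/20 | 9.0 | 5.0 | 12.0 | 6.6 |
| 90/10 | 12.0 | 6.6 | 16.0 | 8.8 |

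**Sensitivity to q.** With q = 30%, 50% or 70%, the centre gap in progression, (1 − q)(hB − hA), is 14, 10 or 6 points for a 20-point admission gap, and 7, 5 or 3 points for a 10-point gap. At a 70/30 split these are multiplied by 0.4, giving 1.2 to 5.6 points.

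**Sensitivity to independence.** If the extra admissions fell mainly on patients who also meet another criterion, the progression difference would be smaller. If they fell mainly on other patients, it would be larger, up to the hospitalization difference itself.

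**Effect of matching on site.** For any shares p1 and p2 from centre B, the hospitalization difference is (p1 − p2)(hB − hA). Exact matching on site forces p1 = p2, so this bias becomes zero whatever the admission gap.

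No figure is offered for progression as a predictor of mortality, because the documents give nothing to base one on.

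**The case against.** **A reader might infer that the protocol contradicts itself** by criticising hospitalization in the MRSS and then using it. That is too strong. The Discussion raises a potential concern about hospitalization as an input to a prognostic score. The matched sub-analyses use it as an outcome, and RISE has no hospitalization item (Table 2). One can hold both positions. The tension is closest where progression is itself used as a predictor of mortality. What stands is narrower: the authors recognise that admission practice varies, and their matching does not allow for it.

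**A reader might infer that admission practice at the centres is being scored as disease progression.** The documents do not show this. Nothing says that the two centres admit differently, and both are tertiary ILD referral centres. Many respiratory admissions reflect real worsening. Nor does anything show that group membership follows site. Drug choice is a plausible route, but the documents give no reason why emphysema, autoimmune markers or HRCT pattern should differ by centre. The supportable wording is that it can happen.

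**The larger figures need strong imbalance.** This is correct. At 55/45 the progression difference is about 1 point, and at 50/50 it is zero.

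**A condensed article may leave site adjustment to a fuller document.** This is partly right. Predictors of hospitalization are to be examined, and multivariable Cox models are planned. Neither excludes site, although neither promises it. The matching factors, however, are listed explicitly, and that list is what needs changing.

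**A reader might conclude that group comparisons should rest on progression without hospitalization.** That would discard an event that matters to patients, and the site problem does not require it: matching or stratification deals with the bias described.

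**Conclusion.** The concern holds in a limited form. The stated matching rule leaves the five comparisons of progression and hospitalization open to confounding by site, in a two-country study whose authors acknowledge that admission criteria vary. Bias arises only if both group membership and admission practice differ by site, and the documents establish neither. Its size is therefore unknown. It is zero with balanced sites. Under the assumed admission rates of 25% or 20% against 40%, with 45% meeting another criterion independently, it reaches 6.6 to 8.8 points for progression and 12 to 16 points for hospitalization at a 90/10 mirror-image split. Only secondary endpoints are involved. Three-year LTx-free survival does not include hospitalization, so the primary endpoint is unaffected.

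**What to change.** 1. In Secondary endpoints, add participating site as an exact-match or stratification factor in each of the five matched comparisons of time to progression and hospitalization incidence. This would also cover any site difference in referral for LTx assessment, another component that may depend on local practice.
2. Stratify by site the analysis of clinical progression as a predictor of mortality.
3. Keep the stated five-event composite as the main definition of progression, and report progression without the hospitalization component as a sensitivity analysis.
4. Add a sentence relating the Discussion's remark on admission criteria to the study's own use of hospitalization.

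The cost is small. Site is known for every patient and hospitalizations are already recorded, so no new data are needed. Matching becomes slightly harder, with some possible loss of matched patients, and the sensitivity analysis will have fewer events than the main analysis.
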